## **Sampling and Size Calculation**

The sample size was calculated based on the primary outcome measure (6MWT). A recent systematic review of prehabilitation in patients undergoing major abdominal surgery reported significant improvement in 6MWT, with a mean difference of 29.4 meters (95% CI: 5.6 to 53.3 meters;  $p = 0.02$ ) compared to standard care [31]. The estimated standard deviation was approximately 101.6 meters, corresponding to an effect size (Cohen's  $d$ ) of 0.29. Using this effect size, with  $\alpha$  of 0.05 and power of 80%, the required sample size was calculated to be 54 participants. Allowing for a 30% dropout rate, a total of 70 participants (35 per group) will be recruited. Sample size calculation was performed using G\*Power version 3.1.9.7.

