The level of significance is set at  $p < 0.05$ . Effect sizes will be determined using Cohen's  $d$ , with values of 0.2, 0.5, and 0.8 indicating small, medium, and large effects, respectively [62]. Additional logistic regression will be used to determine preoperative, perioperative and postoperative risk factors associated with the development of respiratory complications. This will be an exploratory analysis, which may identify trends of predictors reported in the literature having an individual effect on postoperative respiratory complications. For all tests conducted, a  $p$  value of  $< 0.05$  (two-sided) will be considered statistically significant, and mean differences (95% CI) will be reported. The results of this study will be reported in accordance with the CONSORT 2010 guidelines.

|                                                                  | STUDY PERIOD                   |                                 |              |                                     |                                               |                                   |                              |
|------------------------------------------------------------------|--------------------------------|---------------------------------|--------------|-------------------------------------|-----------------------------------------------|-----------------------------------|------------------------------|
|                                                                  | Enrolment
& allocation      | Baseline                        | Intervention | Post-
intervention
assessment | Follow up                                     | Follow up                         | Follow up                    |
| TIMEPOINT                                                        | February
2025- July
2026 | 3-5 week
before
operation | 2- 4 weeks   | Preoperatively                      | Post-
operatively
prior to
discharge | 4-6 weeks
post-
operatively | 3 months post
operatively |
| Eligibility screen                                               | X                              |                                 |              |                                     |                                               |                                   |                              |

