**ETHICAL APPROVAL OF PROPOSAL AMENDMENT**

Research Title : The Effectiveness of High-Intensity Interval Training versus Moderate Intensity Continuous Training in Prehabilitation among Patients Undergoing Major Abdominal Surgery

Ethics Ref. No. : JEP-2024-527

Approval period : 06 November 2024 – 05 November 2026

The above matter mentioned and your letter dated 07 July 2025 is referred.

2. The Research Ethics Committee, The National University of Malaysia has approved your proposal amendment as title above in the Research Ethics Committee Meeting No. 15/2025 dated 24 July 2025 as below:

- i. The sample size has been revised from 60 to 70 participants following a recalculation (page 25).
- ii. The inclusion criterion requiring participants to achieve a six-minute walk distance (6MWD) of at least 300 meters has been removed. This change is due to the limited number of eligible patients and the absence of this criterion in previous related studies (page 31).
- iii. The age range for participants has been updated from 18–75 years to 18 years and above to allow for a wider recruitment pool (page 24).
- iv. The screening for the Hospital Anxiety and Depression Scale (HADS) has been removed, as HADS is included as one of the outcome measures in the study (Page 31)

3. Please submit any **Adverse Events Report, Progress Report every 6 months and Final Report** upon completion of the research to the Research Ethics Committee. The minute of meeting no. 15/2025 dated 24 July 2025 is attached for your reference.

Thank you.

Yours sincerely,

[figure not shown]  

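### The 30% dropout allowance was added to the required 54 rather than divided out, so 70 recruits leave 49 and not 54

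*Protocol*

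**What the plan says.** The sample size for the randomised trial rests on the six-minute walk test. The protocol takes a prehabilitation effect from a systematic review, "with a mean difference of 29.4 meters", and adds that "The estimated standard deviation was approximately 101.6 meters", giving d = 0.29. With alpha 0.05 and 80% power, "the required sample size was calculated to be 54 participants". The next sentence makes the dropout adjustment: "Allowing for a 30% dropout rate, a total of 70 participants (35 per group) will be recruited".

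The 70 is then used throughout. Blinding and allocation specifies five blocks of 14 and 70 envelopes, and the timeline sections plan for 70 participants. The ethics committee's amendment approval of July 2025 records that "The sample size has been revised from 60 to 70 participants following a recalculation". That letter does not mention the 54 or the dropout rate. It shows that the committee was given 70 as a calculated figure.

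**The concern.** A 30% dropout rate means that 30% of the people recruited are lost. To have a given number left, the target must be divided by 0.70. The protocol multiplied it by 1.30, which always gives too few. The paragraph therefore contradicts itself: at the dropout rate it allows for, the recruited number falls below the number it says is required.

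At stake is a design property that a reader or committee will take from the paragraph, namely that the trial can lose 30% of its patients and still have what it needs. It cannot. The step would also carry over to any corrected requirement, so repairing the 54 alone would leave it in place.

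**Working it through.** **Inputs.** From Sampling and Size Calculation: requirement 54 in total, dropout 30%, recruitment 70 (35 per group), mean difference 29.4 m, SD 101.6 m, alpha 0.05, power 80%. From Statistical analysis: two-sided testing.

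**1. Reproducing the protocol's figure.**
- 54 × (1 + 0.30) = 70.2, stated as 70.
- The Phase 1 survey does the same: its 57 becomes 74 for 30% non-response, and 57 × 1.30 = 74.1.
- The protocol gives no other rule for the allowance and no other reason for 70.

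**2. What 70 recruits leave at 30% dropout.**
- 70 × (1 − 0.30) = 49.
- Shortfall: 54 − 49 = 5, and 5/54 = 9.3%.

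**3. What 54 after 30% dropout needs.**
- 54 / (1 − 0.30) = 77.1.
- Check: 77 × 0.70 = 53.9, just short; 78 × 0.70 = 54.6, enough.
- So 78 recruits, 39 per group, which is 8 more than planned.

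**4. The dropout that 70 can absorb.**
- 1 − 54/70 = 16/70 = 22.9%.

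**5. Consequence for power, if 54 did give 80%.**
- The standardised signal at 54 is 1.960 + 0.842 = 2.802.
- It shrinks with the square root of the sample size: 2.802 × √(49/54) = 2.669.
- Power = Φ(2.669 − 1.960) = Φ(0.709) = 76%, a loss of about 4 points.

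**6. Consequence for precision.** This uses the protocol's SD, equal arms and a simple two-group comparison of means. The half-width of the 95% CI is 1.96 × 101.6 × √(2/n per arm).
- 54 patients (27 per arm): 1.96 × 101.6 × 0.2722 = 54.2 m.
- 49 patients (24.5 per arm on average): 1.96 × 101.6 × 0.2857 = 56.9 m.

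**7. Relation to the 54 itself.** With d = 29.4/101.6 = 0.289, a two-sided two-group comparison at 80% power needs 2 × (2.802/0.289)² ≈ 188 per arm, or 376 in total.
- At that effect, power by the normal approximation is 18.5% with 27 per arm and 17.2% with 24.5 per arm.
- If 376 became the requirement, adding 30% would give 376 × 1.3 = 488.8, so 489. Dividing gives 376 / 0.7 = 537.1, so 538. The same slip would then cost 49 recruits.

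**The case against.** The arithmetic is not in dispute; the weight is. Four points can be made for the protocol.

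- **Analysis population.** All randomised patients are analysed by intention to treat with multiple imputation, and the outcome is measured at five time points. A patient lost late still contributes earlier walk distances, so 49 counts patients with complete follow-up and is not the number analysed. That is a fair description. But imputation does not restore outcome information that was never collected, and the protocol itself treated dropout as a loss to be made up by recruiting more.
- **Wording.** "Allowing for a 30% dropout rate" might mean no more than a 30% margin on top, as in the survey calculation. The protocol nowhere says that 54 will remain. Yet the text names a dropout rate, and on the add-on reading the protection is still only about 23%, so the sentence misstates what the design tolerates.
- **The 54 matters far more.** This stands. At the stated effect size the slip costs about 1.3 percentage points of an already very low power. The 4-point loss applies only if 54 is valid for some test whose settings the protocol does not give; some repeated-measures settings come near 54, but none is stated. Correcting the inflation does not show that 54 is adequate.
- **Power on 49.** A power figure for 49 cannot sensibly be written until the basis of the 54 is settled. This also stands, and the fix below allows for it.

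**Conclusion.** The concern holds. On the protocol's own figures, 70 recruits leave 49 patients at 30% dropout, 5 short of the stated 54. The 54 is reached only if dropout is 22.9% or less, and keeping it at 30% would take 78 recruits.

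The size is modest: 8 recruits, about 4 points of power if 54 gave 80%, and a confidence interval about 5% wider (√(54/49) = 1.05). The count of 49 assumes that dropout means no outcome at the time point of interest. The power and precision figures assume equal loss in the two arms and a simple two-group comparison. The point is independent of whether 54 is right, and it should be corrected because the paragraph is wrong as written.

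**What to change.** Restate the dropout sentence in Sampling and Size Calculation along these lines: *Seventy participants (35 per group) will be recruited. At 30% dropout, 49 would have complete data; 54 would remain if dropout does not exceed about 23%.*

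Add a precision statement for 49. With the protocol's SD of 101.6 m, the expected 95% CI half-width for the between-group difference is about 57 m. Leave any power statement on 49 until the basis of the 54 is corrected, and make the two changes together. Any new requirement should be divided by 0.70, not multiplied by 1.30.

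Recruitment, envelopes and blocks can stay as they are. The cost is a short text change, notified to the ethics committee as its approval letter requires, and a stated tolerance that is less favourable (23% instead of 30%). The power statement is not a one-line change, but that work belongs to the correction of the 54.

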## **Study Method**

### **Intervention care group (HIIT)**

Participants in the intervention group will receive the same care as the standard care group. Additionally, for aerobic exercise this will be a moderate intensity which is 55-75% of maximum heart rate (MHR) in week one, with graduation to high intensity in week two on > 80% of MHR [24]. Aerobic exercise training (eg: Treadmill, Cycle ergometer, body weight exercises) 1-3 times per week (30 minutes) for an overall duration typically 2-4 weeks prior to the date of surgery. Patients' Maximum Heart rate ( $210 - \text{age}$ ) and Karvonen Formula will be used for the targeted heart rate. Patients' heart rate will be monitored along the aerobic training using a smartwatch. However, those patients who are on beta-blockers or with underlying cardiac conditions, training intensity will be guided by the Rating of Perceived Exertion (RPE) between 16-18 RPE score, with appropriate adjustments made to ensure safety. The interval training will be 30-60 seconds of high-intensity training with 1- 2 minutes of active recovery (light activity or complete rest) between intervals to facilitate recovery. This will be repeated for a total of 5-10 cycles [32].

In addition to aerobic training, participants will receive the same progressive resistance exercise and inspiratory muscle training, with intensity matched to that of the standard care of

MICT group. Aim for a total session duration of about 20-30 minutes, including warm-up and cool-down. This includes 10-15 minutes of HIIT, depending on the patient's tolerance. Sessions will be done 1-3 times per week, with rest days in between to allow for recovery. Participants will also receive an illustrated handout to guide continued training support by caregivers, including recommendations on maintaining a standard amount of aerobic and strength exercise per week. A detailed session attendance checklist and vital signs will be recorded at each session to monitor adherence.

All other aspects of patient care such as preoperative management, general anaesthesia, intraoperative ventilation settings, fluid administration, prophylactic antibiotic use, pain management, management of lines and drains, general nursing care, and discharge planning will be administered at the discretion of nurses and physicians in accordance with routine clinical practices at hospital for both groups.

### **Standard Care for Control Group (MICT)**

This will be a tailored and supervised by a single physiotherapist (more than 10 years clinical experiences in cardiorespiratory) in outpatient hospital setting. Participants will engage in an aerobic (moderate intensity continuous training), strengthening exercise and inspiratory muscles training program prior to the date of their surgery.

For aerobic exercise this will be a low intensity in week one with graduation to moderate intensity. Moderate intensity continuous training (MICT) will allow 55-75% of maximum heart rate (MHR) [33]. Aerobic exercise training (eg: treadmill, cycling, walking exercise) 1-3 times per week (60 minutes) for overall duration typical 2-4 week prior to date of surgery. Patients' Maximum Heart rate (210-age) and Karvonen Formula will be used for targeted heart rate. Patients' heart rate will be monitored along the aerobic training using smart watch. However, the Karvonen formula may not be suitable for all patient populations, particularly those on beta-blockers or with underlying cardiac conditions. In such cases, training intensity will be guided the RPE between 10-13 RPE score, and appropriate modifications will be made to ensure safety. This approach allows for individualized intensity adjustment while maintaining the safety and effectiveness of the intervention.

For the progressive resistance exercise, the following muscle groups will be targeted: biceps brachii, triceps brachii, pectoralis major and minor, latissimus dorsi, deltoid and rhomboids using free weights. The intensity will be 70-80% of estimated 10 repetitions

maximum. The load not provided joint pain or severe muscle fatigue and/or arm fatigue on RPE of 10-13 on 6-20 RPE score [60]. Aim for a total session duration of about 45-60 minutes, including warm-up and cool-down. This includes 30-45 minutes of MICT, depending on the patient's tolerance. Sessions will be done 1-3 times per week [60].

In addition to the PVC weighted bar, we also used different types of resistance training such as band, dumbbells, kettlebells. Inspiratory muscles training will be given 20 mins per day with 30% of maximum inspiratory pressure (MIP) [14].

Participants will also be given an illustrated handout to assist further training support by the carer (advice regarding maintaining a set amount of aerobic/strength exercise per week standard [1][2][14]. Detailed session attendance checklist and vital sign will be recorded for every attendance for adherence.

|                        | HIIT                                                                                                                                 | MICT                                                                              |
|------------------------|---------------------------------------------------------------------------------------------------------------------------------------------|------------------------------------------------------------------------------------------|
| Duration and Intensity | 10- 15 minutes

Alternating short bursts of high-intensity exercise (>80% of peak heart rate) with periods of low-intensity recovery. | 30-45 minutes

Continuous moderate-intensity exercise (55-75% of peak heart rate). |
| Borg's RPE             | 16-18                                                                                                                                       | 10-13                                                                                    |
| Borg's dyspnea         | 5-8                                                                                                                                         | 3-4                                                                                      |
| Talk test              | Difficult to speak without pausing a breath every few words                                                                                 | Able to speak in full sentence                                                           |
| Type of exercise       | Start warm-up for 5-10 minutes.

Jogging and higher speed cycling.                                                                    | Walking, cycling, stair climbing                                                         |

Table 2: The table shows the differences between HIIT and MICT that will be conducted in our setting

### Flowchart for Patient Recruitment and Screening

1. Start - Begin the recruitment and screening process.

## 2. Patient Eligibility Screening

Step 1: Check if the patient is awaiting major abdominal surgery.

Yes: Proceed to the next step.

No: Exclude from study.

Step 2: Check if patients Medically unstable or severe comorbidities that contraindicate exercise (e.g., unstable cardiovascular disease), Impaired cognition or confusion and impaired vision, cognition or physical impairment (UL and LL) in functional task components

Step 3: Conduct additional baseline assessments (e.g., medical history, strength, flexibility, respiratory function) for patients included in the study.

Step 4: Obtain informed consent from eligible patients.

Step 5: Randomize patients into the HIIT or MICT intervention groups.

End -Complete the screening and recruitment process.

## Data collection

Demographic data and preoperative, intraoperative, and postoperative variables will be collected from participants and their medical records. Baseline assessments will be conducted 4 ( $\pm 1$ ) weeks in outpatient setting following referral for exercise based prehabilitation prior to date of surgery. Follow up assessment will continue to 2 days ( $\pm 1$ ) before operation in the inpatient setting, prior to discharge, 4 -weeks, and 12-week post operatively. These follow-ups will take place in the research room within the physiotherapy unit.

All measurements will be conducted by an independent, trained assessor located off-site, who will remain blinded to group allocation. Face-to-face administration of follow-up tests and questionnaires will be performed by outcome assessors at four time points: preoperatively, prior to discharge, 4 weeks, and 3 months postoperatively, to maintain consistency across participants.

Post-hospital discharge follow-ups will be contacted via phone. Participants who cannot be reached by phone for 14 consecutive days from the scheduled assessment date will be considered lost to follow-up for post-discharge outcomes.

## **Primary outcome measures**

### **The 6-Minute Walk Test (6MWT)**

The 6MWT is a widely used measure to assess the submaximal level of functional capacity [34]. The test involves walking back and forth along a 30-meter indoor track for as many laps as possible within a 6-minute period [35,36]. Following the American Thoracic Society (ATS) guidelines, the test will be conducted before initiating prehabilitation, with the better result from two attempts recorded as the baseline measurement [37]. Participants will be informed of the elapsed time at the end of each minute during the test, but no additional encouragement will be provided [37].

### **Maximal Inspiratory Pressure**

Inspiratory muscle strength will be assessed by measuring the maximum inspiratory pressure (MIP) generated at the mouth using the PowerBreathe K2 device. Patients will be seated in an upright position and instructed to exhale fully to their residual volume before performing a maximal and rapid inspiratory effort lasting 3 seconds. The highest 1-second average value from each trial will be recorded. To ensure reliability, three consistent measurements (defined as having a coefficient of variation <10%) will be selected from 5 to 8 maximal trials, with each trial separated by a 60-second rest interval [38].

## **Secondary outcome measures**

### **1 Minute Sit to Stand Test (1MSTST)**

The 1MSTST is recognized as a tool for assessing functional status and predicting fall risk. It has shown a good correlation with exercise capacity in patients with chronic obstructive pulmonary disease (COPD) [39]. Studies have demonstrated a significant correlation between the number of repetitions completed in the 1MSTST and essential functional outcomes in patients with COPD, including the 6-minute walk distance (6MWD), quadriceps muscle strength, and physical activity levels [39, 40, 41]. These findings suggest that the 1MSTST may serve as a valid measure of exercise capacity following respiratory rehabilitation, especially in

populations with comorbid of pulmonary complications, which is common in patients with abdominal surgery.

### **Short Physical Performance Battery (SPPB)**

The SPPB will be used to assess lower extremity physical performance status. It is an objective outcome measures of balance, lower extremity strength, and functional capacity which includes three domains (walking, sit-to-stand and balance) [42]. SPPB had an excellent interrater reliability (ICC = 0.92) among people with respiratory condition [43]. Besides, it may serve as a reliable surrogate endpoint for all-cause mortality in clinical trials aiming to evaluate the efficacy of specific treatments or rehabilitation programs in improving health outcomes [44].

### **The Hospital Anxiety and Depression Scale**

Anxiety and depression will be measured using the 14-item Hospital Anxiety and Depression Scale (HADS), which comprises two subscales: one for anxiety (HADS-A) and one for depression (HADS-D), each containing seven items [45]. Each item is scored on a 4-point Likert scale ranging from 0 (not present) to 3 (maximum), with a maximum subscale score of 21 points [46]. A cut-off score of  $\geq 8$  points will be applied to identify cases of anxiety or depression, as this threshold has been shown to optimize sensitivity and specificity for both subscales [46]. The HADS is a validated and reliable instrument, with Cronbach's  $\alpha$  values of 0.81 for HADS-A and 0.88 for HADS-D [46,47]. It has been widely translated and extensively utilized in international research [46,48], demonstrating high internal consistency in inpatient populations, including those undergoing median sternotomy [48].

